### Hb 5-11 gm/dl - iron tablet or syrup and folate tablet for 14 days dosed according to age (Hb < 5 gm/dl – referral to hospital.

*Procedures for household visits.*  Field workers will visit each enrolled child every 2weeks. S/he will ask about episodes of diarrhea since the last visit as well as current episodes. S/he will also record symptoms of acute respiratory illness and malaria, as well as any health seeking and medications resulting from these illnesses (Appendix C). S/he will ask about recent or current fever and any health seeking and medications resulting from the recent or current fever. S/he will also inquire about any use of zinc in the last two weeks. The number of days of zinc and number of pills of zinc will be documented. The interviewer will ask to see the zinc blister pack and record how many pills are remaining.

*Administration of zinc*

In the villages/clusters randomized to no home zinc, parents will be instructed by the field workers to take their children to the clinic if they have diarrhea, defined as an episode having 3 or more loose or watery stools (+/-) blood in a 24 hour period. At the clinic, the child will be evaluated by a clinical officer. If the child meets the above definition of diarrhea, they will be given zinc and ORS as described below.

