In the villages/clusters randomized to home zinc, parents will be supplied with one 10-day blister pack of zinc and 3 satchets of ORS for each child in the house under 5 years of age. Zinc packs and ORS satchets will be given once every 2 months, regardless of whether the zinc was used in the previous month. Parents will be given instructions on how to use zinc and ORS at the beginning of the study and every 2 months thereafter when the zinc is given to them by a village reporter (a traditional birth attendant) or a community health worker. Parents in these villages/clusters will also be instructed to take their children to the clinic if they have diarrhea. They will be specifically instructed that taking zinc and ORS should not prevent them from taking their child to the clinic. Particular emphasis will be made that any child with diarrhea, *and* another symptom such as fever or cough, should definitely be taken to the clinic – that zinc is not adequate treatment for a child with fever or cough, who might need an antimalarial or an antibiotic. If the field worker on his biweekly visit finds out that the mother has given zinc to a child not meeting the diarrhea case definition, he will not tell the mother to stop the course of zinc. This is for several reasons. First, the field worker will not be medically trained and so will not be trained to apply the case definition of diarrhea. Second, diarrhea is a symptom taken by history, so that if the mother reports the child has diarrhea, the field worker will not really be able to assess the accuracy of that symptom. Third, there will be no adverse effects from the course of zinc – daily zinc supplementation regardless of illness has been shown to be beneficial in some studies (Zinc Investigators Collaborative Group 1999, Zinc Investigators Collaborative Group 2000). However, the field worker will encourage all mothers of children with diarrhea, especially those with fever, cough or another symptom, to go to the clinic to be seen by a clinical officer. The use of zinc for episodes of diarrhea will be evaluated on a biweekly basis based on the data collected by the field workers to assure that zinc is not being given alone when the child has other symptoms, such as fever and cough. If a significant number of mothers are giving zinc inappropriately without seeking care for other symptoms, further education in the use of zinc in the home will be given. Community health workers or village reporters, different from the field workers who do the biweekly visits, will make home visits every month during the first 3 months of the study to ensure that mothers understand the proper use of zinc and ORS for treatment of diarrhea. After the first three months, the village reporter or community health worker will visit the home every 3 months. On each home visit, the village reporter will ask some questions to assess whether mother is using zinc correctly (appendix L).

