### History of fever in the last 24 hours

- Cough and difficult or fast breathing

Care at Lwak clinic for children in the study will be free of charge. Children in the study will be identified at the clinic by an identification card.

*Clinic visits.* All study children will be identified in the clinic by an identification card. They will be seen by a clinical officer hired by the study. Diagnosis and treatment will be according to standard protocols used for childhood illness in peripheral health facilities in Kenya (IMCI. Zinc and low osmolarity ORS will be administered according to MOH protocol. For children in the home zinc group, the clinical officer will inquire if the child is already taking zinc for that episode of diarrhea. If so, then no more zinc will be given. If not, then a 10 day course of zinc will be given. Bloody diarrhea will be treated with nalidixic acid. Uncomplicated malaria will be treated according to KMOH guidelines, artemether/lumefantrine (coartem) as of June 2006. Pneumonia not requiring referral to hospital will be treated with cotrimoxazole or amoxacillin. Children meeting criteria for referral to the hospital according to IMCI guidelines will be hospitalized at Lwak Hospital, and transferred to Bondo District Hospital or Nyanza Provincial Hospital, if appropriate treatment cannot be given at Lwak..

Children with a recent history of or documented fever will have a blood smear for malaria taken. If the results of the blood smear are positive for malaria, the child will be treated for malaria as outlined above. Blood smears will be read by a microscopist at the clinic.

A questionnaire will be filled out for study children who visit the clinic. The questionnaire will ask about symptoms, duration of illness and health-seeking behaviour (Appendix E).

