**Baseline measurements.**

27. Weight ____ Kg 27. Height ____ cm

28. Malaria smear  Positive  Negative  Not Done

28b. If positive, malaria parasites per 500 wbc _____

1. Hemoglobin ____gm/dl  Not done
2. Blood drawn for zinc level  Yes  No  Not done

**Appendix C. Household Morbidity Form** Interviewer code:______

Child’s first/Christian name _______________________ Juok/middle name___________________________ Last/father’s name _____________________

DSS ID number: . --- *(Use temporary permanent ID if child does not yet have a permanent ID, which should be village, compound, house and “99” for individual ID number. )*

*(Put 1 in days in which symptom was present, 0 if symptom not present, 9 if don’t know). Ask about every symptom. On the day of visit measure temperature and respiratory rate and evaluate for dehydration if current diarrhea, and chest indrawing and grunting if cough or difficulty breathing.*

Month:______________________

| *Symptom* | *If yes to symptom* | *1* | *2* | *3* | *4* | *5* | *6* | *7* | *8* | *9* | *10* | *11* | *12* | *13* | *14* | *15* | *16* | *17* | *18* | *19* | *20* | *21* | *22* | *23* | *24* | *25* | *26* | *27* | *28* | *29* | *30* | *31* |
| --- | --- | --- | --- | --- | --- | --- | --- | --- | --- | --- | --- | --- | --- | --- | --- | --- | --- | --- | --- | --- | --- | --- | --- | --- | --- | --- | --- | --- | --- | --- | --- | --- |
| *Diarrhea* |  |  |  |  |  |  |  |  |  |  |  |  |  |  |  |  |  |  |  |  |  |  |  |  |  |  |  |  |  |  |  |  |
|  | *# stools* |  |  |  |  |  |  |  |  |  |  |  |  |  |  |  |  |  |  |  |  |  |  |  |  |  |  |  |  |  |  |  |
|  | *Bloody?* |  |  |  |  |  |  |  |  |  |  |  |  |  |  |  |  |  |  |  |  |  |  |  |  |  |  |  |  |  |  |  |
| *Vomitting* |  |  |  |  |  |  |  |  |  |  |  |  |  |  |  |  |  |  |  |  |  |  |  |  |  |  |  |  |  |  |  |  |
|  | Everything? |  |  |  |  |  |  |  |  |  |  |  |  |  |  |  |  |  |  |  |  |  |  |  |  |  |  |  |  |  |  |  |
| *Unable to drink/breastfd* |  |  |  |  |  |  |  |  |  |  |  |  |  |  |  |  |  |  |  |  |  |  |  |  |  |  |  |  |  |  |  |  |
| *Fever* |  |  |  |  |  |  |  |  |  |  |  |  |  |  |  |  |  |  |  |  |  |  |  |  |  |  |  |  |  |  |  |  |
| *Cough* |  |  |  |  |  |  |  |  |  |  |  |  |  |  |  |  |  |  |  |  |  |  |  |  |  |  |  |  |  |  |  |  |
| *Difficulty breathing/fast breathing* |  |  |  |  |  |  |  |  |  |  |  |  |  |  |  |  |  |  |  |  |  |  |  |  |  |  |  |  |  |  |  |  |

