**Part 4: Treatment**

Analgesics (Panadol, Aspirin) 

Amodiaquine 

Coartem (lumafantrin/aretmether 

Quinine 

SP 

Septrin (cotrimoxazole) 

Penicillin V 

Amoxacillin 

Gentamicin 

Nalidixic acid 

Ciprofloxacin 

Cloxacillin 

Tetracycline 

Antihelminthic (mebendazole/albendazole) 

ORS 

Salbutamol 

Piriton (chloropheniramine, antihistamine) 

Other: ___________________________

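### The two-weekly household form and the clinic form lack the zinc fields the protocol text calls for, so total zinc days and the between-arm comparison of zinc use would be incomplete

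*Protocol*

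**What the plan says.** Under Procedures for household visits, the field worker sees each enrolled child every two weeks. On zinc, the text says "S/he will also inquire about any use of zinc in the last two weeks", then "The number of days of zinc and number of pills of zinc will be documented", and finally "The interviewer will ask to see the zinc blister pack and record how many pills are remaining". Compliance monitoring adds a count of remaining pills at days 7 and 14.

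At the clinic, for children in the home-zinc group, "the clinical officer will inquire if the child is already taking zinc for that episode of diarrhea"; a 10-day course is given if not. In clinic-only villages the clinic is the planned source of zinc (Administration of zinc).

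Three uses of these data are planned:
- Secondary objective 5 compares zinc use between the arms: frequency and adherence, recipients, and indications.
- The prevalence analysis includes a Poisson regression on each child's total zinc days, in the zinc villages.
- A safety-minded review checks that zinc is not given alone when other symptoms are present: "The use of zinc for episodes of diarrhea will be evaluated on a biweekly basis based on the data collected by the field workers".

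**The concern.** The text promises a zinc record at every two-weekly contact and a zinc inquiry at the clinic, but the forms for those contacts have nowhere to write either. Exposure that is not collected during the year cannot be recovered by any later analysis plan.

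At stake are the completeness of the zinc-days variable, the arm comparison in objective 5, and the ability to see zinc passing from home-zinc households into clinic-only villages. Such sharing would weaken the contrast between arms. The form gap does not cause it, but would leave it without a structured record unless it happened within a followed-up diarrhoea episode.

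**Working it through.** The plan gives no figure to reproduce here, so the check sets each form against the text.

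| Form | When completed | Zinc items on it | What it lacks |
| --- | --- | --- | --- |
| Appendix C, household morbidity form | Every two weeks, both arms | None. Symptom, clinic-visit and examination rows only | Zinc days, pills taken, pills remaining, reason |
| Appendix D, diarrhoea follow-up | New episodes found at home or in the clinic, both arms | Daily 'Took zinc' row; vomiting after zinc | Pills remaining; cough |
| Appendix E, clinic sick visit | Clinic visits, both arms | None, apart from a mention in the adverse-event question | 'Already taking zinc' question; zinc in the treatment list |
| Appendix L, village reporter survey | Home visits described for home-zinc villages | Any use since last visit, recipient, reason, tablets used from last pack | Dates of use; earlier packs; clinic-only villages |

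Appendices B, F and J also mention zinc. They do so once at baseline, after an incident, or at the blood sample, so none tracks use over the year.

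**Appendix C.** Its instructions go into detail elsewhere ("On the day of visit measure temperature and respiratory rate and evaluate for dehydration if current diarrhea"), so the absence of a zinc row is not a matter of brevity. It has a row for visits to Akala although the study clinic is Lwak, which suggests it was not updated for this design.

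**Appendix E.** Part 4 lists ORS and 16 drug entries, down to "Antihelminthic (mebendazole/albendazole)", then a free-text 'Other'. Zinc can only be written there.

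**What Appendix D covers.** The Follow-up of cases of diarrhea section sends a visit to every new episode identified at home or in the clinic. Zinc taken after a clinic visit is therefore recorded by day in both arms. The form's instruction allows visits at days 3, 7 and 14, so a 10-day course is spanned if the form is completed at day 14. A child given zinc without diarrhoea gets no Appendix D.

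**What Appendix L covers.** Visits are monthly for 3 months, then every 3 months.
- Months 1, 2, 3, 6, 9, 12: 6 visits.
- If the two-monthly pack distributions also use the form, months 4, 8 and 10 are added: 9 visits.
- Two-weekly visits over the same year: 52 / 2 = 26.

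Packs are issued every 2 months while later visits are 3 months apart, so a count from the last pack need not cover the interval.

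**Ceilings on the contacts involved** (not counts of lost records). The Sample size section expects about 3,000 children; the Abstract says about 1,300. The Sample size section assumes 3.6 episodes a year. Equal arms are my assumption.
- Two-weekly visits without a zinc field: 3,000 × 26 = 78,000, or 1,300 × 26 = 33,800.
- Clinic-only-arm episodes: 3,000 × 3.6 / 2 = 5,400, or 1,300 × 3.6 / 2 = 2,340.

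**The case against.** The strongest reply is that the collection plan is already in the body text and only the appendix lags. The zinc sentences cite no form, the forms are to be field tested (Data collection), and two other forms do record zinc. Much of this stands, and it rules out several stronger readings that a reader might infer.

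- *That zinc outside followed-up episodes is not captured at all.* Appendix L asks about use, recipient and reason (including fever and cough) whether or not there was diarrhoea. In home-zinc villages capture is sparse, not absent.
- *That clinic zinc is not captured.* Intake is on Appendix D for clinic-identified episodes. What is missing is a structured dispensing item.
- *That the review of zinc given alone cannot be done.* As stated it concerns zinc used for diarrhoea episodes. Appendix D gives zinc, fever and clinic attendance, Appendix C gives cough, and both carry the child's DSS number. Joining them is ordinary data management. Only zinc given without diarrhoea has no field-worker record, although the text foresees field workers finding it.
- *That sharing into clinic-only villages distorts the zinc-days regression.* That analysis is confined to the zinc villages.
- *That tens of thousands of records are lost.* Most two-weekly visits would involve no zinc, and the Justification section says most children with diarrhoea do not reach a health facility.

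The reply does not remove the mismatch. No other two-weekly form is shown, Appendix L is completed by people the protocol distinguishes from the field workers, and it cannot supply dated zinc days or a comparison between arms.

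**Conclusion.** The point holds as a contradiction between text and forms, with consequences for secondary analyses.

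- Appendices C and E lack the zinc items that the household and clinic sections require. The promised counts of pills remaining have no field on Appendices C, D or E.
- Total zinc days in the zinc villages would miss use outside followed-up episodes.
- Objective 5 would compare arms on unequal information: Appendix D in both, Appendix L in one. Adherence would rest on caretaker report without the planned pill check on these forms.
- Zinc shared into clinic-only villages would have no structured record outside followed-up episodes, and clinic dispensing would rest on free text.

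The amount of zinc missed cannot be computed, because the protocol does not say how much would be taken outside followed-up episodes. The primary outcome data are unaffected: diarrhoea days are on Appendix C in both arms.

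This assumes that Appendix C is the only two-weekly form, that Appendix L is used only where its visits are described, and that Appendix D is completed at day 14 as its instruction allows.

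**What to change.** Before the study starts:
- **Appendix C**, identically in both arms: a daily 'took zinc' row, reason for zinc, pills given and pills remaining.
- **Appendix D**: pills remaining at each follow-up visit.
- **Appendix E**: in Part 2, whether the child is already taking zinc for this episode and its source (home pack, clinic, other); in Part 4, zinc with tablets dispensed.
- **Analysis text**: state that zinc days for objective 5 and for the zinc-days regression are derived from these fields, with Appendix L as supporting information in home-zinc villages.

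The cost is revising three forms, on paper or on the handheld devices if adopted, and a little more interview time per visit. Nothing in the design, sample size or primary analysis changes.

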Update on Amendment March 26, 2007: The procurement of zinc has been delayed by the Kenya MOH because of lack of competitive bidders in the tender sent out for this in late 2006. Now it is likely zinc will not arrive in Kenya until late 2007. Until zinc arrives and becomes part of the essential drug kit, the study will provide zinc treatment in the clinic to children coming in with diarrhea. The indications and dosages will those recommended by WHO and the same as will be adopted by the Kenya MOH. Until zinc becomes part of the essential drug kit and available to all children in the clinic, only children who are enrolled in this study will receive zinc. When zinc does become part of the essential drug kit and available in the clinics, the children in the study will continue to receive zinc as before, and nonstudy children will also receive it.

Justification for the study. The use of zinc to treat or prevent diarrhea in Kenya has not been studied. The results of such a study among Kenyan children will be important in providing relevant information to the Ministry of Health to make policy decisions and in building within-country advocacy for scale-up of zinc use and whether to adopt a policy of community use of zinc, in addition to use in the health facilities, for diarrhea treatment. Because access to health care is poor in much of Kenya and most children with diarrhea do not go to health facilities, home-based treatment of diarrhea with zinc could be reach more children, and treat and prevent more diarrhea.

Statement of the null hypothesis. In villages in Western Kenya where children with acute diarrhea are treated (self-prescribed zinc/provided in home) with zinc and ORS at home in addition to the clinic, the prevalence of severe acute diarrhea will be the same as in villages where children with acute diarrhea are treated with zinc and ORS at the clinic only.

Objectives

*Primary*

1. To assess if access to zinc treatment for diarrhea in the home in addition to zinc treatment of diarrhea in the clinic leads to a greater reduction in the prevalence of diarrhea than giving zinc for treatment of diarrhea in the clinic only

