*Inclusion criteria.* All children 2 to 59 months of age in households within selected villages that are already enrolled in the IEIP morbidity surveillance project (KEMRI SSC # 985; CDC IRB # 4678) will be eligible for enrollment. Children born into the study area after the start of the study will also be eligible for enrollment after they reach 2 months of age. Recruitment and enrollment will be done by field workers working for the study, who will read the consent form to guardians of all eligible participants that explains the study.

*Exclusion criteria.* Children under 2 months of age will not be eligible for enrollment, until they reach 2 months of age as the role of zinc has not been well-studied in neonates. Children of parents who do not give written informed consent for their participation will not be enrolled.

*Randomization.* This will be a cluster-randomized study. Thirty-three villages in Asembo participating in the morbidity surveillance (see below) will be selected to participate in this study. The villages will be randomized as 16-17 villages for zinc + ORS at home and clinic villages and 16-17 villages and ORS at clinic only villages. All eligible and participating children within a village will get the same treatment. A form will be filled out to keep track of the enrollment (appendix K). See figure.

Select 33 villages in Asembo closest to Lwak clinic

Obtain community approval

of chiefs and subchiefs

Home Zinc 10 days + low osm ORS

Referral to clinic

15 villages

No home zinc or ORS

Referral to clinic

15 villages

Continue biweekly household

visits for incident and prevalent

diarrhea, ARI, fever illness

Incident diarrhea episodes

Obtain parental consent of

children < 5 years

Baseline survey of prevalence

of diarrhea, ARI, malaria

Randomly assign to home zinc

and no home zinc villages

biweekly household

visits for incident and prevalent

diarrhea, ARI, fever illness

*Baseline survey and measurements.* All enrolled households will have a baseline survey done at the beginning of the study. The survey will collect the following data (Appendix B).

- Diarrhea management and care seeking practices
- Household characteristics
- Socio-demographic characteristics of household
- Water & sanitation exposures/practices
- Knowledge & attitudes about zinc, other micronutrients
- Height & weight
- Insecticide treated bednet use
- ORS awareness/use
- Antimicrobial use

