
At the clinic, the child will be evaluated by a clinical officer. If the child meets the above definition of diarrhea, the clinical officer will inquire if they are already taking zinc for this episode of diarrhea. If they are not already taking zinc and ORS, he will give them zinc and ORS as described below.

Along with instructions regarding how to take zinc, parents will be instructed in the use of ORS and proper fluid management (i.e. encouragement of breastmilk, if breast-feeding, ORS, or food-based fluids, such as soup, enriched uji). Recommended ORS amounts will follow KMOH guidelines. In the first 4 hours, the amount of ORS recommended will be as follows:

| Age | Up to 4 mos | 4-11 mos | 12 mo – 2 yr | 2-5 yrs |
| --- | --- | --- | --- | --- |
| Weight | < 6 kg | 6-<10 kg | 10-<12 kg | 12-19 kg |
| In ml | 200-400 | 400-700 | 700-900 | 900-1400 |

This should be followed by replacement for each loose stool as follows: up to 2 years of age 50-100 ml per stool and 2 years or more 100-200 ml.

Zinc will be administered using the same formulation in the home and in the clinic. Zinc will be administered in the form of a dispersible tablet of zinc-sulfate, 20 mg. A half-tablet, 10 mg, will be administered to children between 2 and 5 months of age. A full 20 mg tablet will be given to children > 6 months of age. The tablet will be dissolved in water, ORS or breast milk and administered to the child. . Mothers will be instructed on using clean water to dissolve tablets for remaining doses. Children who vomit after taking their dose of zinc will not be given another dose that day. The mother will be instructed how to administer the zinc tablet. Zinc will be given once daily for 10 days total. Zinc will be provided in a dispersible zinc tablet and packaged in a 10 tablet blister pack. If the child is holding down fluids and has not vomited in the past 2 hours, then zinc treatment should be started, otherwise the caretaker will be instructed to wait until this occurs.

*Referrals.* If on the day of the field interviewer’s visit, the child has any of the following conditions on the day that the field worker visits the home, the child will be referred to the health clinic

- Diarrhea with
  - moderate to severe dehydration (defined according to IMCI as having 2 or more of the following symptoms: lethargic/unconscious, sunken eyes, not able to drink or breastfeed, skin pinch goes back slowly, restless/irritable) or not able to take ORS

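### Home zinc packs are counted for every under-5 in the house, although children under 2 months are excluded and no zinc dose is stated for them

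*Protocol*

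**What the plan says.** Four places in the Protocol bear on who gets home zinc.

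- **Supply (Administration of zinc).** Parents in home-zinc villages receive "one 10-day blister pack of zinc and 3 satchets of ORS for each child in the house under 5 years of age". Supply repeats: "Zinc packs and ORS satchets will be given once every 2 months, regardless of whether the zinc was used in the previous month". After the first three months, the same section has the village reporter or community health worker visiting every 3 months.
- **Eligibility (Inclusion and Exclusion criteria).** Entry is open to "All children 2 to 59 months of age in households within selected villages" that are already in the morbidity surveillance. The lower limit is explicit: "Children under 2 months of age will not be eligible for enrollment, until they reach 2 months of age", and the reason given is "as the role of zinc has not been well-studied in neonates". Children born during the study wait until that age. Children whose parents do not give written consent are not enrolled.
- **Dosing (Administration of zinc).** The youngest group with a zinc dose is the one in this sentence: "A half-tablet, 10 mg, will be administered to children between 2 and 5 months of age". The ORS table has a band reaching below 2 months, so the missing entry concerns zinc only.
- **Follow-up (Procedures for household visits; Follow-up of cases of diarrhea).** The two-weekly visits that ask about zinc are to enrolled children. The day-7 visit, with its side-effect questions, follows from diarrhea found at those visits or in the clinic.

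**The concern.** The instruction that a distributor would actually follow counts packs over a wider group than the one the trial may enrol. It takes in infants under 2 months, and siblings whose caretaker refused consent. For the infants, the Protocol gives its own reason for caution and then supplies a product for which it states no dose at that age.

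What is at stake is mainly eligibility and safety. Study-supplied zinc would sit in the home in the name of a child the trial has excluded. Any use would fall outside the follow-up designed to catch side effects. There is also a smaller record-keeping matter: an infant in a home-zinc village could enter the study at 2 months having already taken zinc, and entry procedures for late enrolees do not clearly capture this.

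**Working it through.** No sample size, power or alpha figure is involved, and the Protocol states no figure to reproduce. The check has two parts.

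**1. The texts side by side**

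| Function | Lower age | Enrolment or consent condition |
| --- | --- | --- |
| Enrolment | 2 months | written consent required |
| Zinc dose | 2 months | none stated |
| Home pack supply | none | none |

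The supply row does not match the other two, and no other section limits it.

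**2. How many infants a literal reading would reach**

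Inputs from the Protocol: ineligible window 2 months; supply interval 2 months; later home-visit interval 3 months; follow-up 1 year; about 1,300 children (Abstract) or about 3,000 under-5s (Sample size); about half of the 33 villages in the home arm.

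Assumptions: births spread evenly; a flat age distribution under 5; and a share *s* of newborns living in houses that already receive packs. The documents do not give *s*, so 40% to 100% is used.

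*Share of newborns meeting a round while under 2 months* = min(1, window / interval).

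- 2-month interval: min(1, 2/2) = 100%. With rounds at months 0, 2, 4, 6, 8 and 10, every birth up to month 10 is met. Over all births in the 12 months the share is 10/12 = 83%, or 100% if there is also a round at month 12.
- Packs travelling with the visits (months 0, 1, 2, 3, 6, 9): births in months 0–3, 4–6 and 7–9 are met, so (3 + 2 + 2)/10 = 70% of births in months 0–10. In steady state the share is 2/3 = 67%.
- Multiplying by *s*: 40–100% under the 2-month interval, and 27–67% under the 3-month interval.

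*Number of packs in a year*

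- Births in home villages: 1,300/5/2 = 130, or 3,000/5/2 = 300.
- Cross-check by rounds: infants under 2 months are 2/60 of under-5s. For 650 to 1,500 children in home villages that is about 22 to 50 per round, and six rounds give 130 to 300.
- Upper end (all reached, *s* = 100%): about 130 to 300.
- Lower end (1,300 children, two-thirds reached, *s* = 40%): 130 × 2/3 × 0.4 ≈ 35.

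If supply were confined to eligible, enrolled children, the count would be zero by construction.

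**The case against.** The best reply is that the supply sentence is loose shorthand. The Randomization paragraph speaks of eligible, participating children in a village getting the same treatment. The enrolment form (Appendix K) is itself headed for children under 5, although enrolment starts at 2 months. The distributor's form (Appendix L) is completed for a named child and separates the participant from a sibling. This makes a narrower intent plausible. It does not remove the problem, because none of these texts limits the pack count or tells the distributor to withhold a pack.

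Several stronger readings are tempting and are not supported:

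- **That a standing rule reserves zinc for enrolled children.** The words "only children who are enrolled in this study will receive zinc" come from the March 2007 update. They apply only until zinc joins the essential drug kit, in a paragraph about zinc given in the clinic. They are weak support, and the conflict stands without them.
- **That field workers must let an ineligible infant's course run.** The instruction not to stop zinc concerns children who do not meet the diarrhea definition. It does not address age or enrolment.
- **That excluded infants are dosed and go unseen.** A pack in the house is not a dose given. Some use could come to light: Appendix L asks who took the pills, surveillance visits cover adults and children, and adverse events may be raised on any two-weekly round. What is missing is the dedicated follow-up.
- **That nearly every newborn is supplied.** This needs a strict 2-month round reaching every newborn's house.
- **That the primary comparison is biased.** The primary objective is the effect of access to home zinc, so earlier access in home villages is arguably part of the contrast. No size of bias can be derived from the document.

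**Conclusion.** The contradiction is real and should be corrected. Pack supply has no lower age and no enrolment or consent condition, while enrolment has both and the zinc dosing text starts at 2 months. Followed as written, the supply instruction issues packs for infants whom the Protocol excludes for a stated safety-related reason, and for children without consent. The consequence is a risk of use outside eligibility.

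The scale for infants runs from about 35 packs a year to about 130–300. It depends on which interval governs hand-out, on the share of newborns in supplied houses (assumed 40–100%), on which of the Protocol's two population figures applies, and on a flat age distribution. The Protocol reports infant mortality of 120 per 1,000, so births may be somewhat more than one-fifth of under-5s; the counts are orders of magnitude. Siblings without consent cannot be counted from the document. No statistical figure in the Protocol changes.

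**What to change.** - Reconcile the Inclusion and Exclusion criteria with the supply and dosing text in Administration of zinc, so that one age range and one enrolment condition govern consent, pack supply and dosing instructions. The sponsor's clinical team sets both; this review does not say which passage should prevail.
- Apply the reconciled condition when packs are handed out, using the enrolment record already kept through Appendix K.
- Appendix B item 17 already asks whether the child has ever been given zinc, but the baseline survey is placed at the start of the study. Ask the item at entry for infants enrolled later, so that zinc taken before enrolment is recorded.

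The cost is a few words of protocol text, use of an existing record at distribution, and one existing question asked at a further time point. No change to sample size or analysis is needed.
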